#### Safety observation measures

2.4.3

(1)General physical examination items, such as body temperature, heart rate, respiration, blood pressure, and blood sugar.(2)Possible adverse events and the incidence of adverse events.

### CT Imaging evaluation method

2.5

The CTPI images collected in all cases will be evaluated blindly by 2 physicians who have more than one diagnosis. After jointly determining the perfusion abnormal area and reaching an agreement, the region of interest (ROI) is manually drawn. The ROI selects the center of the lesion, and simultaneously draws the contralateral mirror area on the centerline symmetry axis. When the symmetry area is an abnormal perfusion, the normal area of the contralateral same-layer perfusion parameter map is selected as the contralateral mirror area. CBV, TTD, and MTT values. Infarct focus was based on review of MRI DWI high signal area. The degree of stenosis of the responsible vessels was also evaluated.

### Randomization and blinding

2.6

The random method will use the closed envelope method. We will refer to the random number table to generate random arrangements for the intervention and control groups. The corresponding treatment serial number is sealed and placed in a light-tight envelope to form a random letter. Patients will be randomly assigned to the intervention group or the control group in the order of the included cases. In addition, at the time of drug distribution, all tested drugs must be accompanied by a corresponding numbered emergency letter before distribution. Medicines will be distributed according to the group and medicine number assigned to each patient's visit number. The number of the drug must remain the same during clinical observations.

### Statistical analysis

2.7

SPSS for windows 24.0 statistical analysis software will be used for calculation, and normality test and homogeneity test of variance will be performed on each group of data. For measurement data in which the data conforms to the normal distribution, we will use the mean ± standard deviation. For nonnormally distributed measurement data, the median ± quartile interval is used. General data comparison between the two groups using independent sample T test. Comparisons before and after treatment will be performed using t test for paired data. One-way analysis of variance will be used for comparison between groups. X^2^ test will be used for count data, and nonparametric rank sum test will be used for rank data. All statistical tests are two-sided. *P* < .05 indicates a significant difference.

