**Methods/design::**

This study plan randomly divided eligible acute cerebral infarction patients into two groups. Patients in the control group will be treated with conventional Western medicine; patients in the intervention group will be treated with traditional Chinese medicine cooperative therapy on the basis of conventional Western medicine. The curative effects will be selected before treatment, 2 weeks after treatment, and 3 months follow-up. The changes in CT imaging evaluation, NIHSS score, and BI index of the two groups of patients will be observed.

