### Study design and settings

2.1

A brief flowchart of the entire study is shown in Figure 1. We will perform a 2-group, randomized, single-blind, placebo-controlled, and multi-center trial that will evaluate the efficacy and safety of TCM cooperative therapy for patients with ACI. This study will use a completely random grouping and parallel control observation design method. We will ensure the balance of the baseline data of the two groups through a sufficient sample size and a completely randomized grouping method. The protocol includes elements recommended in the Standard Protocol Items: Recommendations for Interventional Trials checklist (Additional file 1).

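### Section 2.7 lists within-arm paired t tests beside a baseline-unadjusted between-arm ANOVA and does not say that the between-arm comparison decides efficacy

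*Protocol article*

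**What the plan says.** The design is a two-arm randomised comparison: "We will perform a 2-group, randomized, single-blind, placebo-controlled, and multi-center trial" (section 2.1). The abstract sets three assessment times: "The curative effects will be selected before treatment, 2 weeks after treatment, and 3 months follow-up". It says that changes in CT imaging, NIHSS and Barthel Index (BI) will be observed, so baseline values of all three are collected.

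Section 2.7 then fixes these methods for measurement data:

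- General data: "General data comparison between the two groups using independent sample T test".
- Within an arm over time: "Comparisons before and after treatment will be performed using t test for paired data".
- Between arms: "One-way analysis of variance will be used for comparison between groups".
- Sidedness: "All statistical tests are two-sided", with one significance threshold of P < .05 for every test.

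No covariate is named. The section does not say whether the ANOVA is run on follow-up values or on changes, or which of the tests supports a claim of efficacy. Section 2.3.1 gives both arms the same basic Western treatment. Section 2.1 leaves baseline balance to complete randomisation and an unspecified but sufficient sample size.

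**The concern.** A paired test asks whether an arm changed, not whether TCM changed it. Patients enter within 72 hours of onset (section 2.2.2), both arms are treated, and some recovery is to be expected in each. A significant before-after result in the TCM arm is therefore likely even if TCM does nothing. A significant result in the TCM arm beside a non-significant one in the control arm is also common by chance. If both kinds of test carry the same P < .05 label and neither is ranked, such a pattern can be reported as benefit.

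The between-arm test is the right comparison, but it is set up inefficiently. With two arms, one-way ANOVA is the ordinary two-sample t test. It makes no adjustment for baseline, although baseline NIHSS may run from 6 to 22 points (section 2.2.2) and baseline perfusion values are measured in every patient. What is at stake is precision, and correction for whatever chance imbalance occurs.

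**Working it through.** **Inputs.** From the article: two parallel arms, baseline and follow-up values of each outcome, paired t test within arms, one-way ANOVA between arms, two-sided 5%. The article gives no sample size, SD, effect size or correlation, so there is no stated figure to reproduce. Assumed for illustration: 30, 60 or 100 per arm; correlation r between baseline and follow-up of 0.3 to 0.7; common recovery of 0, 0.3 or 0.5 SD; where a sample size is shown, a treatment effect of 0.5 SD.

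**1. One-way ANOVA with two groups.** F = t². On a generated data set of 40 per arm, F = 0.6355, t² = 0.6355, and both P values are 0.4278. The two procedures are the same test.

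**2. Paired test when TCM has no effect.** Simulation of 20,000 trials per setting, r = 0.5, the same recovery in both arms:

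| Recovery | n per arm | TCM arm significant | TCM arm only |
|---|---|---|---|
| 0 | 30 / 60 / 100 | 5% / 5% / 5% | 5% / 5% / 5% |
| 0.3 SD | 30 / 60 / 100 | 36% / 62% / 84% | 23% / 23% / 13% |
| 0.5 SD | 30 / 60 / 100 | 75% / 97% / 99.9% | 18% / 3% / 0.1% |

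Check of the last column: the arms are independent, so the TCM-only probability is p(1 − p). For 0.3 SD: 0.360 × 0.640 = 0.23; 0.624 × 0.376 = 0.23; 0.844 × 0.156 = 0.13.

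**3. Between-arm ANOVA in the same simulations.** It rejected in 4.7% to 5.2% of trials in every setting, on follow-up values or on changes. Shared recovery cancels.

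**4. Precision of the between-arm contrast.** With equal SDs, the variance relative to a follow-up-only analysis is 1 for follow-up only, 2(1 − r) for change and 1 − r² for ANCOVA. The ratio of ANCOVA to change is (1 − r²) / [2(1 − r)] = (1 + r)/2.

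| r | Change | ANCOVA | ANCOVA ÷ change |
|---|---|---|---|
| 0.3 | 1.40 | 0.91 | 0.65 |
| 0.5 | 1.00 | 0.75 | 0.75 |
| 0.7 | 0.60 | 0.51 | 0.85 |

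**5. The same in patients.** Patients per arm for an effect of 0.5 SD with 80% power:

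| r | Follow-up only | Change | ANCOVA |
|---|---|---|---|
| 0.3 | 63 | 88 | 58 |
| 0.5 | 63 | 63 | 48 |
| 0.7 | 63 | 38 | 33 |

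**The case against.** The best defence is that section 2.7 already has a between-arm test in a randomised design, that the paired tests are assigned only to before-after comparisons, and that a condensed article may leave the choice of covariates to an analysis plan. Part of this stands.

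- A reader might infer that efficacy rests on the paired tests. The article does not say so. Its fault is that it does not rule them out.
- A reader might infer that the ANOVA also counts spontaneous recovery as evidence. It does not: recovery common to both randomised arms cancels, and the error rate stays near 5%. Chance imbalance is already covered by that error rate.
- A reader might infer that baseline is discarded. This is exact only if the ANOVA uses follow-up values. The abstract speaks of changes, and on that reading baseline is used, though less efficiently than by ANCOVA and, for r below 0.5, with more variance than follow-up alone.
- A reader might quote the largest gain. At r = 0.7, ANCOVA is worth 96% more patients against follow-up only (1/0.51), but only about 18% more against change scores (0.60/0.51).
- A reader might add that non-normal data get only a different summary: "For nonnormally distributed measurement data, the median ± quartile interval is used". The section assigns a rank sum test to rank data, which can cover NIHSS and BI. A fallback test for the CT parameters is detail commonly left to an analysis plan, so this is not part of the point.

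What the defence does not remove is that paired t tests and an ANOVA without covariates are stated methods, not omissions, and that they stand unranked under one significance rule.

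**Conclusion.** The point holds in limited form. Section 2.7 leaves open that a within-arm P value is read as evidence for TCM, and its between-arm test is valid but less precise than the collected data allow.

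The size of the first part depends strongly on the assumptions. Over the settings examined with some recovery, the TCM arm is significant in 36% to 99.9% of trials with no TCM effect. The more misleading pattern, significance in the TCM arm alone, ranges from 23% down to 0.1%, because with strong recovery or large arms both arms become significant. The size of the second part is a variance reduction of 9% to 49% against a follow-up-only analysis, or 15% to 35% against a change-score analysis, for r between 0.3 and 0.7. Sample size, correlation and recovery are all assumed, since the article states none of them. This is an improvement that should be made, not a flaw that invalidates the between-arm comparison.

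**What to change.** In section 2.7:

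1. State that the between-arm comparison is the sole basis for conclusions on efficacy.
2. Replace the one-way ANOVA with ANCOVA of the follow-up value on arm and the baseline value of the same variable. For the CT and BI outcomes, add baseline NIHSS. For the NIHSS outcome, it is already the baseline covariate and enters once.
3. Report the adjusted difference between arms with its 95% CI.
4. Report before-after changes in each arm as description, without P values.

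The cost is a few sentences. The outcome baselines are already planned, NIHSS is needed for eligibility, and the named software, SPSS, fits ANCOVA. The article says that recruitment has not started and that ethics review is still to come (sections 2.9 and 3.1), so the change can be made before any data exist.

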### Data management

2.8

Information obtained from the evaluation of each participant will be recorded on a paper print-out. The information will then be handwritten on a paper document case report form and entered into an Excel file for future statistical analyses. In accordance with the Personal Information Protection Act, the names of all participants will not be disclosed, and a unique identifier number given during the trial will be used to identify participants. All of the participants will be informed that the clinical data obtained in the trial will be stored in a computer and will be handled with confidentiality. The participants’ written consent will be stored by the principal investigator.

### Ethics

2.9

This study will be approved by the Ethics Committee of Dongzhimen Hospital Affiliated to Beijing University of Chinese Medicine. The study will be conducted under the Declaration of Helsinki principles, as well as following the norms of good clinical practice. Recruitment of patients has not started in this study. The study plan will be submitted to the ethics committee of the Ethics Committee of Dongzhimen Hospital Affiliated to Beijing University of Chinese Medicine for review. We will not start recruiting participants without the consent of the ethics committee.

## Discussion

3

The early diagnosis of ACI is of great significance to improve the prognosis of patients and save patients’ lives.^[10]^ Because only when the condition is found and diagnosed early in the onset of cerebral infarction (within 6 hours) can subsequent treatment such as intravenous thrombolysis be advanced. In this way, we can grasp the optimal timing of thrombolysis and reduce the degree of brain tissue damage.^[11,12]^ In addition, it is clinically recognized that changes in cerebral blood flow can feed back pathological changes in human brain tissue.^[13]^ For example, cerebral hemodynamic changes in patients with cerebral infarction have obvious characteristics. It is mainly manifested in local neurochemical changes in the early stages of onset.^[14]^ In order to ensure the local normal blood supply, the cerebral blood vessels will inevitably show a state of compensatory expansion. Corresponding resistance to cerebrovascular circulation will be significantly reduced. Imaging showed increased cerebral blood flow and prolonged mean transit time of contrast medium.^[15]^ When the vasodilation reaches the upper limit, cerebral blood flow will decrease. Once the state persists for more than 6 hours, it means that the blood supply to the brain is greatly reduced. At this time, cerebrovascular dilatation reaches a decompensated state, which in turn causes irreversible damage. Some scholars have stated in research that comprehensively grasping the patient's brain imaging diagnostic information in the early stages of onset will help physicians to correctly judge the condition such as whether the central neuron is necrotic, whether there are penumbras in the surrounding area, and the area of the penumbra area is geometric.^[16,17]^ Take first aid measures symptomatically. It is not difficult to see that clarifying the lesions and their changes in cerebral blood flow is very important to reverse the outcome of brain tissue. And how to obtain more comprehensive and valuable information about blood flow in living cells has always been the focus of investigation in imaging medicine.

ACI belongs to the category of “stroke” in TCM.^[18]^ Mostly caused by overwork, poor diet and emotional damage. Studies have shown that traditional Chinese herbal medicines has the effects of increasing high-density lipoprotein, reducing low-density lipoprotein, regulating blood lipids, stabilizing plaque, and protecting vascular endothelium.^[19–21]^ In addition, in the early stages of ACI, Chinese herbal medicines can remove free radicals and reduce damage caused by free radicals.^[22,23]^ This can reduce blood viscosity, thereby improving the oxygen carrying capacity of red blood cells and preventing brain tissue damage.^[24,25]^ In summary, this study plans to use TCM cooperative therapy to treat ACI and use CTPI imaging to evaluate the efficacy. We aim to provide higher evidence-based medical evidence for TCM treatment of ACI. And clarify the application value of CTPI in the diagnosis and efficacy evaluation of ACI.

### Trial status

3.1

At the time of manuscript submission, recruitment for the study is not yet started.
